## Abstract

**Background:**

There is evidence to suggest that delivery of diabetes self-management support by diabetes educators in primary care may improve patient care processes and patient clinical outcomes; however, the evaluation of such a model in primary care is nonexistent in Canada. This article describes the design for the evaluation of the implementation of Mobile Diabetes Education Teams (MDETs) in primary care settings in Canada.

**Methods/design:**

This study will use a non-blinded, cluster-randomized controlled trial stepped wedge design to evaluate the Mobile Diabetes Education Teams' intervention in improving patient clinical and care process outcomes. A total of 1,200 patient charts at participating primary care sites will be reviewed for data extraction. Eligible patients will be those aged ≥18, who have type 2 diabetes and a hemoglobin A1c (HbA1c) of ≥8%. Clusters (that is, primary care sites) will be randomized to the intervention and control group using a block randomization procedure within practice size as the blocking factor. A stepped wedge design will be used to sequentially roll out the intervention so that all clusters eventually receive the intervention. The time at which each cluster begins the intervention is randomized to one of the four roll out periods (0, 6, 12, and 18 months). Clusters that are randomized into the intervention later will act as the control for those receiving the intervention earlier. The primary outcome measure will be the difference in the proportion of patients who achieve the recommended HbA1c target of ≤7% between intervention and control groups. Qualitative work (in-depth interviews with primary care physicians, MDET educators and patients; and MDET educators’ field notes and debriefing sessions) will be undertaken to assess the implementation process and effectiveness of the MDET intervention.

**Trial registration:**

ClinicalTrials.gov NCT01553266

## Background

Diabetes mellitus is a chronic illness that requires a lifelong commitment to complex lifestyle modifications involving nutrition management, a physically active lifestyle, regular self-monitoring of blood glucose and adherence to medications and/or insulin therapy. Proper management of these lifestyle modifications have been shown to reduce the risk and progression of diabetes complications
[1-6]. Achieving and sustaining effective management is challenging; more than half of those living with diabetes in Canada are unable to meet the recommended target for glycemic control (≤7% hemoglobin A1c (HbA1c))
[7]. As a result, diabetes self-management support (DSMS) is recommended by Canadian clinical practice guidelines for the management of diabetes as a valuable resource that supports and teaches patients the skills to actively participate in the management of their illness
[8].

DSMS is a collaborative process through which people with, or at risk for, diabetes gain the knowledge and skills needed to modify behavior and successfully self-manage the disease and its related conditions. It is an interactive, ongoing process involving the person with diabetes (and possibly the caregiver and/or family) and a diabetes educator(s), and focuses on essential self-care behaviors, such as healthy eating, being active, monitoring blood glucose, taking medication, problem solving, healthy coping and reducing risks of further complications
[9]. DSMS primarily relies on patients and diabetes educators to define management issues, set priorities, establish collaborative goals, identify barriers, create a management plan and problem-solve to maintain optimal management
[10,11]. The few studies that exist on the delivery of DSMS in primary care have found that DSMS has numerous benefits on patient clinical and care process outcomes, such as an improvement in patient knowledge
[12-14]; a reduction in body weight
[13], HbA1c
[12-16], cholesterol
[14-17], fasting blood glucose
[13,18], self-blood glucose monitoring
[16] and blood pressure
[18]; and improved primary care physician (PCP) adherence to diabetes clinical practice guidelines
[14,17]. However, none of these studies have been conducted within a Canadian setting.

Many diabetes education programs (DEPs) across Ontario and Canada are starting to provide outreach services by creating collaborative partnerships with local PCPs, and establishing mobile diabetes education teams (MDETs) that deliver DSMS to patients and provide diabetes training and support to PCPs within primary care sites. Models of care that integrate multidisciplinary teams have been shown to improve patient access to DSMS
[19] and increase physician support to reduce clinical inertia in the area of diabetes management in primary care
[20-24]. Furthermore, there is growing evidence that inter-professional collaboration (IPC), whereby professionals from different health disciplines collaborate together to achieve a shared goal, such as quality patient care
[25], can improve patient care processes and health outcomes
[26-42]. Thus, to manage diabetes effectively, alternative models of practice that integrate inter-professional teams may be required to reduce the burden of diabetes.

This protocol is for the evaluation of the implementation of MDETs in primary care in Canada. This model of practice supports PCPs at various primary care sites to assist in and share the care and management of patients with diabetes by offering a MDET (one registered nurse (RN) and one registered dietitian (RD)) onsite, one to four times a month based on patient volume (see Table 
1 for an overview of the MDET intervention). The proposed MDET intervention is informed by the five components of the Chronic Care Model (CCM)
[19]: (i) Organization of integrative patient health care; (ii) Forming community linkages; (iii) Encouraging self-management support; (iv) Providing decision support; and (v) Delivery system redesign (see Table 
2). This article describes the non-blinded, cluster-randomized trial stepped wedge design used in the three-year evaluation study of the MDET intervention in primary care.

**Table 1 T1:** Mobile Diabetes Education Team (MDET) intervention components, timelines and content

**Intervention component**	**Timelines**	**Content**
RN initial visit	Patient’s first visit with RN, one hour	**Assessment:** Time-span with diabetes; diabetes knowledge; recent hospital admissions; medication regime and adherence; lab blood work review; medical history; blood pressure; foot exam; capacity for SBGM and/or results review; current exercise regime; presence of diabetes complications; risk management for new and existing acute and long-term complications; proper identification of diabetes.
		**Education:** What is diabetes?; how medications work; signs and symptoms of high and low blood sugars; how to reduce long-term complications; benefits of exercise; SBGM technique and timing; how to interpret SBGM results; sharps disposal; stress management; foot care.
		**Teach as needed:** Insulin time action; insulin administration and technique; titrating doses; sick day management; travel glucagon and ketones.
RD initial visit	Patient’s first visit with RD, one hour	**Assessment:** Effects of food, exercise and medications on blood glucose levels and cholesterol; lab blood work review; weight history and goals; fast food consumption; meal composition and timing; specialty foods, supplements, and alcohol use; food allergies; disordered eating.
		**Education:** Healthy eating guidelines; meal planning, food choices and portion size; carbohydrate load and consistency; major food nutrients; specialty food and sweeteners; fiber, fats, sodium, and alcohol; eating out.
		**Teach as needed:** Carbohydrate counting; glycemic index; insulin carbohydrate ratio.
Action plan and goal setting	At initial MDET visits, and ongoing	MDET helps patient find behaviors they would like to initiate or change; patient and MDET collaboratively create action plan and set goals. This may include a referral to a local DEP for additional support (for example, cooking demos, and so on). Goals are then shared with the PCP.
Collaborative patient care/Patient case conferencing	Following each patient visit with MDET	MDET communicates with PCP through face-to-face meetings or using a communication tool to review major obstacles to good diabetes control and make recommendations about medication changes to help improve control for the patient. Goals are decided upon by the patient as what they would like to work on before the next visit, and are reinforced by the PCP on following visits.
MDET follow-up visits	30 minutes x 3 visits over 1-year period	**Assessment:** Patients’ success in achieving established goals; future goals; SBGM results and recent blood work to determine diabetes control; effectiveness of medication and lifestyle changes.
		**Education:** Teach topics listed in RN and RD initial visit guidelines, based on identified issues from first initial visit, patient questions and follow-up assessment.

DEP, Diabetes education program; MDET, Mobile Diabetes Education Team; PCP, Primary care physician; RD, Registered dietician; RN, Registered nurse; SBGM, Self blood glucose monitoring.

**Table 2 T2:** Chronic Care Model – conceptual framework for MDETs in primary care

**CCM component**	**Operationalization of CCM components**	**Research objective(s)**
Organized integrated patient care	· Diabetes self-management support is being offered in PCPs’ offices for patients with diabetes.	i. Examine the effect of MDETs on patient clinical outcomes.
	· An opportunity is created to promote knowledge exchange and capacity between PCPs and MDETs/DEPs by working together to provide better care for patients in primary care.	ii. Evaluate the effect of MDETs on the quality of care delivered to patients by PCPs.
		iii. Examine the effect of MDETs on physician referral and patient utilization of DEPs.
		iv. Assess the implementation process of the MDET and the degree of IPC between PCPs and MDETs across primary care sites.
Community linkages	· An opportunity is created to promote knowledge exchange and capacity between PCPs and MDETs/DEPs by working together to provide better care for patients in primary care.	iii. Examine the effect of MDETs on physician referral and patient utilization of DEPs.
		iv. Assess the implementation process of the MDET and the degree of IPC between PCPs and MDETs across primary care sites.
Patient self-management support	· Diabetes self-management support is being offered in PCPs’ offices for patients with diabetes.	i. Examine the effect of MDETs on patient clinical outcomes.
Provider decision support	· An opportunity is created to promote knowledge exchange and capacity between PCPs and MDETs by working together to provide better care for patients in primary care.	i. Examine the effect of MDETs on patient clinical outcomes.
	· A communication tool will be used to exchange patient recommendations and treatment plans between MDETs and PCPs.	ii. Evaluate the effect of MDETs on the quality of care delivered to patients by PCPs.
	· Regular case conferences have been agreed upon between MDETs and PCPs after patients’ visits.	iii. Examine the effect of MDETs on physician referral and patient utilization of DEPs.
	· Hard copy of clinical practice guidelines and Diabetes Flow Sheet for Diabetes Management for PCPs.	iv. Assess the implementation process of the MDET and the degree of IPC between PCPs and MDETs across primary care sites
Delivery system re-design	· Diabetes self-management support is being offered in PCPs’ offices for patients with diabetes.	i. Examine the effect of MDETs on patient clinical outcomes.
	· An opportunity is created to promote knowledge exchange and capacity between PCPs and MDETs/DEPs by working together to provide better care for patients in primary care.	ii. Evaluate the effect of MDETs on the quality of care delivered to patients by PCPs.
		iii. Examine the effect of MDETs on physician referral and patient utilization of DEPs.
		iv. Assess the implementation process of the MDET and the degree of IPC between PCPs and MDETs across primary care sites.

DEP, Diabetes education program; IPC, Inter-professional collaboration; MDET, Mobile Diabetes Education Team; PCP, Primary care physician.

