### Scientific hypothesis

We hypothesize that the MDET intervention results in the following outcomes at 12 months:

(i) An improvement in patient clinical outcomes, primarily an increase, or greater proportion, of patients in the intervention group who are at target for HbA1c (≤7%) compared to patients in the control group.(Secondary hypothesis: an increase, or greater proportion, of patients in the intervention group who are at target for low-density lipoprotein (LDL-C) ≤2.0 mmol/L, total cholesterol-high density lipoprotein ratio (TC-HDL ratio) < 4.0, and blood pressure ≤ 130/80 mmHg, compared to patients in the control group).

(ii) An increase in the proportion of PCPs performing patient care processes, according to the Canadian clinical practice guidelines for the management of diabetes, in the intervention group compared to the control group.

(iii) An increase in the proportion of referrals to and patients’ utilization of DEPs in the intervention group compared to one year prior to the start of the intervention.

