### Experimental study design

A non-blinded, cluster-randomized trial stepped wedge design will be used (see Table 
3). Findings from such a study design have been shown to generate sound scientific evidence and may better facilitate the implementation of complex health interventions in practice
[43]. We propose to randomize clusters (that is, primary care sites) and not individuals to the intervention and control group in order to minimize contamination or treatment dissemination between study groups (intervention or control). The presence of a MDET is hypothesized to affect how PCPs care for their patients; and thus, the care patients receive within the same practice site.

**Table 3 T3:** Study design – cluster randomized control trial stepped wedge design treatment schedules

**Randomization of clusters**	**Time 1**	**Time 2**	**Time 3**	**Time 4**	**Time 5**
	**0 months***	**6 months**	**12 months**	**18 months**	**24 months**
Cluster 1	1	1	1	1	1
Cluster 2	0	1	1	1	1
Cluster 3	0	0	1	1	1
Cluster 4	0	0	0	1	1

“*” represents baseline data collection across all sites prior to cluster 1 starting the intervention;

“0” represents control or existing treatment/standard care at primary care sites; “1” represents the MDET intervention; each column represents a data collection point.

Because all PCPs who expressed an interest in this study are eager to have a MDET on site, we plan to use a stepped wedge design to sequentially roll out the intervention. The time at which each cluster begins the intervention is randomized to one of the four roll-out periods (0, 6, 12, and 18 months). The randomization times are separated by six months to allow for assessment of the primary outcome (that is, HbA1c) within a reasonable time after implementation of the intervention

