**Primary care physician (PCP) patient care process measures**		
HbA1c, blood pressure, lipid profile, nephropathy screening (ACR and eGFR) and foot exams/tests	Patient chart data extraction	20 different randomly-selected patient charts per site, per time interval (0, 6, 12, 18 and 24 months of intervention)
Referrals for dilated retinal exam		
Provisions for or recommendations of flu vaccine		
Changes to medication		
Differences in descriptive information across PCPs	PCP questionnaire on descriptive information (that is, sex, age, years practicing, type of practice, number of diabetes patients seen per month)	All PCPs, once
Patients’ experiences and views regarding Mobile Diabetes Education Team (MDET) intervention effectiveness	Patient in-depth interviews	20 randomly-selected patients at 12 months of intervention across sites
Scheduled and attended MDET appointments	Diabetes education program charts/forms	All MDET patients, up to 2 years of intervention

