The proportion of patient care processes completed by PCPs over a one-year period (that is, the percentage of patients with tests for HbA1c, blood pressure, lipid profile, screening for nephropathy (ACR and eGFR), foot exams, referrals for dilated retinal exams, and provisions for or recommendations of the flu vaccine) according to clinical practice guidelines will also be collected from patient charts and compared across study groups. We also plan to document and descriptively examine changes to medication (that is, change in drug, drug dose, and addition of another drug) to assess intensification of medical management and whether the diabetes educators had an influence on PCP practices. Descriptive information (that is, sex, age, years practicing) will be collected for each PCP to further assess differences in patient care processes between study groups.

We will also calculate the percentage of patient referrals by PCPs to hosting DEPs and the onsite MDET and compare this to patients’ actual attendance at DEPs and scheduled MDET appointments. The referral rate to DEPs will be compared to the percentage of referrals from participating PCPs and their patients’ attendance at DEPs a year prior to the start of the intervention. Characteristics available in patient medical charts (that is, sex, age, duration of diabetes, clinical information and so on) will be reviewed and compared between those who were and were not referred to the MDET to better understand PCP referral practices. The number of MDET appointments planned for each patient and the number of MDET visits attended will be collected during the intervention period to examine uptake of the MDET intervention.

Various characteristics of team collaboration will be measured using the Collaborative Practice Assessment Tool (CPAT) Version 2

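### The intervention includes a Diabetes Flow Sheet and care processes are read only from charts, so for note-dependent processes better recording may pass for better care (Objective 2)

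*Protocol article*

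**What the plan says.** Three parts of the protocol article bear on this point.

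- **Intervention.** Table 2 (Background), under provider decision support, lists "Hard copy of clinical practice guidelines and Diabetes Flow Sheet for Diabetes Management for PCPs". In Table 3 (Experimental study design) the code 0 "represents control or existing treatment/standard care at primary care sites".
- **Hypothesis and outcome.** Hypothesis (ii) expects "An increase in the proportion of PCPs performing patient care processes, according to the Canadian clinical practice guidelines". Under Quantitative data collection the measure is "The proportion of patient care processes completed by PCPs over a one-year period". The list covers HbA1c, blood pressure, lipid, ACR and eGFR testing, and also "foot exams, referrals for dilated retinal exams, and provisions for or recommendations of the flu vaccine".
- **Source and analysis.** The data, "according to clinical practice guidelines will also be collected from patient charts and compared across study groups", have no second source. Table 4 likewise gives chart extraction for "Provisions for or recommendations of flu vaccine". Quantitative data analysis applies to Objective 2 the same generalized linear mixed model as to Objective 1: site random, time fixed, and an intervention term.

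The article does not describe the sheet's fields, when it is handed out, whether physicians must complete it, whether it is filed in the chart, or whether control sites already use one.

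**The concern.** A flow sheet is both a prompt and a recording form. If it reaches a site with the intervention and becomes part of the chart, one component of the intervention can change how the intervention's own outcome is ascertained.

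The processes are not equally exposed. HbA1c, lipid, ACR and eGFR tests leave a laboratory report whoever keeps the notes. A foot exam or a vaccine recommendation is usually visible only if someone writes it down. A retinal referral or a vaccine given may also leave a letter or an immunisation record.

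Hypothesis (ii) speaks of "An increase in the proportion of PCPs performing patient care processes". A rise in the note-dependent items would be read as better physician practice, although some of it could be better charting. A larger sample would not help, because the problem lies in what is measured.

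**Working it through.** The plan gives no figure for this point, so there is nothing to reproduce. The check asks whether the model could remove a recording shift, and how large a shift could look.

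**1. Can the model separate the two?** The site effect absorbs what is constant at a site. The time effect absorbs what changes at all sites together. A recording change that begins when a site crosses over has the same 0/1 pattern as the intervention term in Table 3. It is therefore aliased with that term.

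**2. Size of the apparent effect.**
Recorded rate = true rate × probability that a performed process is charted. With no change in care, the true rate cancels:
apparent relative risk = charting probability after ÷ charting probability before.

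The charting probabilities below are assumptions, and so is the true rate of 60% in both conditions.

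| Charting before → after | Recorded rate | Difference | Relative rise |
|---|---|---|---|
| 0.90 → 0.95 | 54% → 57% | 3 points | 5.6% |
| 0.80 → 0.90 | 48% → 54% | 6 points | 12.5% |
| 0.80 → 0.95 | 48% → 57% | 9 points | 18.8% |
| 0.70 → 0.90 | 42% → 54% | 12 points | 28.6% |

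For scale only, the sample size is planned around an 18% relative change in the HbA1c target.

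**3. Would such an artefact be declared significant?** Inputs: 1,200 ÷ (20 × 5) = 12 sites, three per sequence; 20 charts per survey; p = 0.5; two-sided 1% (the plan does not state sidedness); ICC 0.05 (assumed) to 0.39 (Statistical analysis section). The Table 3 footnote places Time 1 before the first sequence starts, so that cell is coded as control.

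- Standard error of the intervention effect: about 0.055 (ICC 0.05) to 0.046 (ICC 0.39).
- Probability of p < 0.01 = Φ(artefact ÷ SE − 2.576).
- 12 points: Φ(0.12/0.055 − 2.576) to Φ(0.12/0.046 − 2.576), about 34% to 52%.
- 6 points: about 7% to 10%.

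**4. Dilution.** Processes are counted over one year and the steps are six months apart, so the first survey after crossover looks back partly on the control period. If that survey shows only half the artefact (assumed), the model estimates about half of it overall. Rejection for the 12-point case then falls to about 7% to 10%, against a nominal 1%.

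**5. Would dropping flow-sheet entries solve it?** No. Take 48% recorded under control and 54% under intervention, from the second row above. If 20% of the charted intervention entries are on the sheet only, the outside-sheet rate is 54% × 0.8 = 43%. If 40% are, it is 54% × 0.6 = 32%. That is a false loss of 5 or 16 points.

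**The case against.** The strongest reply is that the mechanism is inferred. Table 2 says only that physicians receive the sheet. It may stay outside the chart, go unused, or already be in use under standard care. This stands, and it is why the point is conditional: recording may change, and the documents do not show that it does.

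A reader might go further in three ways that the documents do not support.

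- *That the three processes are visible only in notes.* The article does not say how any item is charted, and referrals and vaccinations can leave other traces.
- *That the bias always favours the intervention.* A sheet kept outside the chart, or one that replaces progress notes, could lower what is extracted.
- *That a 12-point artefact would be significant in 45% to 64% of trials.* That range requires the first sequence to be treated at Time 1, contrary to the Table 3 footnote, and the full artefact at once.

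Two further replies have weight. A flow sheet is decision support, so part of a rise may be a real and intended effect; but chart data alone cannot apportion it. Extraction rules also often sit in a manual that a condensed article omits. Even so, the article itself fixes the intervention content, the outcome wording and the single data source, and these together create the ambiguity.

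**Conclusion.** The concern holds in a limited, conditional form. If the flow sheet is new at crossover and is filed in the chart, the note-dependent part of hypothesis (ii) cannot distinguish better recording from better care. Foot exams and vaccine recommendations are the most exposed. The size is unknown: 12.5% and 29% relative rises follow from assumed charting shifts of 80% to 90% and 70% to 90%, before dilution by the look-back.

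The point concerns Objective 2 only. The HbA1c primary outcome is untouched, and laboratory-based processes are far less exposed. It is a cheap improvement to what hypothesis (ii) can conclude and does not show that the planned comparison is invalid.

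**What to change.** 1. Add one extraction field for where each care-process entry was found: flow sheet only, or progress note, letter, immunisation record or laboratory report.
2. Rest the conclusion that physician performance improved on processes with a laboratory trace: HbA1c, lipid profile, ACR and eGFR.
3. Report foot exam, retinal referral and flu vaccine as documentation-sensitive. Give the all-sources count as the upper bound and the count outside the flow sheet as the lower bound. Neither should be the sole measure, because excluding sheet-only entries removes items mainly in the intervention condition.
4. State whether control sites already use a flow sheet and whether the intervention's sheet is filed in the chart. If sites already use an equivalent sheet, or the new one never enters the chart, most of the concern falls away.

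The cost is one extra extraction field, some text in the analysis section, and a firm conclusion that rests on fewer processes. The field is easiest to capture during extraction; adding it later means reopening charts.
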